## Methods

### Design

The study design is a multicenter randomized clinical trial in which several primary healthcare centers in the province of Concepcion, Chile will participate. Randomization will be at the individual level (Figure 1). The randomization will be performed by blocks (each healthcare center will be a block) and will be performed after identification of all the people who have agreed to participate in the study. Two stratifications will be made for each block. The first stratification will be by the type of professional involved and divided into three categories: physicians, health professionals (nurse, midwife, nutritionist, physical therapist, dentist, paramedic, pharmacist, podiatrist), and psychosocial professionals (psychologists and social workers). The second stratification will be by the work sector of each healthcare center. In each stratum, a similar number of people will be randomized for the experimental and control group using the software package “blockrand,” which creates randomizations for block random clinical trials.

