### Procedure

Primary healthcare centers from the province of Concepcion, Chile will be invited to participate. The participation of each center is approved by the Ethical-Scientific Committee of each health service and authorized by their directors. A requirement for the inclusion of a center in the study is the authorization for the participation of health workers in the program sessions during work hours. Various activities will be performed to promote the program in each selected health center and to encourage participation. The program will be implemented in health centers where there are at least 18 people enrolled to permit the randomization of control and experimental groups with at least nine people per group. Given the sizes of the centers, a maximum number of 40 participants will be considered per health center since it is unlikely that there will be more than that number of people enrolled. The randomization process will form groups with 9 to 20 people. All healthcare workers will be invited to participate through informative meetings and flyers distributed in each health center. Once the participants have agreed to take part in the program and have been evaluated, they will be randomized. The initial evaluation (T1) will take 3 weeks, and the implementation of the program will last a total of 8 weeks. The post-test evaluation (T2) will be done during the 3 weeks following the end of the program. Four months after the end of the program, the follow-up evaluation will be performed (T3) (Table 1).

**Table 1 T1:** Study assessment points.

**Measurement**	**Scale**	**T1**	**T2**	**T3**

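### Blocked randomisation within profession and work-sector strata does not ensure the stated minimum of nine per group in a centre that enrols 18 (minor)

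*Protocol article*

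**What the plan says.** Protocol article, Methods, Design: "Randomization will be at the individual level". Each centre is treated as a block, and randomisation "will be performed after identification of all the people who have agreed to participate in the study". The section continues: "Two stratifications will be made for each block". On these it says "The first stratification will be by the type of professional involved and divided into three categories" (physicians, health professionals, psychosocial professionals), and then "The second stratification will be by the work sector of each healthcare center". The balance target is set at the stratum: "In each stratum, a similar number of people will be randomized for the experimental and control group using the software package" blockrand. The section gives no number of sectors, no block length, no rule for strata of odd size and no constraint on the centre total.

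Protocol article, Methods, Procedure: a centre takes part only if at least 18 people enrol, "to permit the randomization of control and experimental groups with at least nine people per group". Enrolment is capped at 40, and the same section states that randomisation will produce groups of between 9 and 20.

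**The concern.** The two sections describe different things. Procedure states a result for the whole centre: 18 enrolled gives nine per group. Design describes a method that works stratum by stratum and aims at similar, not equal, numbers in each. Balance within small strata does not carry up to an exact centre total, because the unpaired people in odd-sized strata can fall on the same side.

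The minimum of 18 has no slack, so any imbalance leaves one arm below nine. The programme is delivered in groups, and control workers receive it later, so a short arm in either direction becomes a programme group smaller than the plan states. Arms also become unequal within the centre.

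**Working it through.** **The plan's own figures.** 18 / 2 = 9 and 40 / 2 = 20. The stated group range of 9 to 20 is therefore half of the enrolment range of 18 to 40. It reproduces, but at 18 only under an exact 1:1 split of the whole centre.

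**Inputs from the article.** Three profession levels (Design); minimum 18 and maximum 40 per centre (Procedure); at least 11 centres (Procedure); 210 participants, or 231 after 10% loss (Power and Data Analyses).

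**Inputs that the article does not give, so assumed.**
- Work sectors per centre, S: 1 to 4.
- The two factors are crossed, giving 3 × S strata.
- Block length: 2, 4, or random among 2, 4, 6 and 8.
- Profession mix: equal thirds, 20/60/20 or 15/65/20.
- Each stratum is randomised on its own, with no correction of the centre total.

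**Stratum size at 18 enrolled.** 18 / (3S) = 6.0, 3.0, 2.0 and 1.5 people for S = 1, 2, 3 and 4.

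**Exact check with blocks of 2.** Each odd stratum leaves one person assigned to either arm with probability 1/2. At 18 enrolled the number of odd strata, k, is even, and P(9:9) = C(k, k/2) / 2^k:
- k = 0: 100%
- k = 2: 2/4 = 50%
- k = 4: 6/16 = 37.5%
- k = 6: 20/64 = 31%
- k = 8: 70/256 = 27%

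**Simulation.** One centre, multinomial stratum counts, 6,000 runs per setting; Monte Carlo standard error at most √(0.25/6000) = 0.6 percentage points. The table gives the percentage of runs with both arms at nine or more for the 20/60/20 mix. Each cell shows blocks of 2 / blocks of 4 / random 2 to 8.

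| Sectors | 18 enrolled | 20 | 21 | 24 |
|---|---|---|---|---|
| 1 | 61.9 / 49.4 / 41.4 | 100.0 / 95.7 / 89.8 | 100.0 / 99.5 / 96.9 | 100.0 / 100.0 / 99.9 |
| 2 | 45.1 / 35.2 / 31.8 | 92.8 / 82.5 / 77.5 | 98.9 / 93.4 / 89.4 | 100.0 / 99.9 / 99.4 |
| 3 | 38.0 / 29.5 / 26.7 | 86.9 / 75.0 / 70.0 | 95.5 / 86.9 / 82.2 | 100.0 / 99.1 / 97.7 |
| 4 | 34.4 / 27.0 / 24.5 | 80.3 / 70.1 / 67.6 | 92.1 / 82.9 / 78.2 | 99.8 / 98.1 / 96.8 |

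Across all three mixes and repeat runs, which agree to within a few points, the ranges are about 25–64% at 18 (1 to 4 sectors). For 2 to 4 sectors they are about 61–93% at 20, 76–99% at 21, and 95% or more at 24.

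**Size of the miss.** At 18 enrolled with 2 to 4 sectors, the smaller arm averages about 7.7 to 8.4 people. With the 15/65/20 mix it holds at least eight in 82–94% of runs with blocks of 2, and in 66–80% with random blocks of 2 to 8.

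**How near the minimum centres will be.** 210 / 11 = 19.1 and 231 / 11 = 21 per centre on average. Eleven centres of 18 would give 198, below both targets, so with 11 centres not all can sit at the minimum.

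**Effect on the trial total.** Over 11 centres of 21 with 2 to 4 sectors, the standard deviation of the overall arm difference is about 6 to 11 people out of 231. The efficiency loss is roughly (difference / total)²: (6/231)² = 0.07% to (11/231)² = 0.23%, which is negligible.

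**The case against.** The best defence is that the article can be read as intending balance at centre level. It calls the centre the block, completes the roster before randomising, and states groups of exactly half the enrolment limits. With the roster in hand, leftovers from odd strata could be paired, and 18 would then always give 9:9. Block length and the handling of odd strata are also details that an article may leave to the full protocol.

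Part of this stands. Independent handling of leftovers is an assumption of the calculation, and the absence of a block length is not itself a fault. But the article does state where balance is sought, which is in each stratum, and how closely, which is similar numbers. It also states a centre-level result that this method does not guarantee. That is a mismatch between two stated rules rather than a missing detail.

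It is also fair to object that the problem is sharpest at exactly 18, that nothing shows how many centres will enrol so few, and that the article attaches no consequence to a group of eight. Those points stand and keep the severity low. The planned averages of 19 to 21 are still within the range where a miss is possible.

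**Conclusion.** The Design and Procedure sections do not fit together as written. Under the stated assumptions, a centre of 18 meets the nine-per-group rule about 25–64% of the time; even in the most favourable setting it misses in more than a third of cases. The problem shrinks quickly as enrolment rises and has nearly gone by 24. The percentages depend on the sector count, the crossing of the factors, the profession mix and the block length, none of which the article gives. The qualitative point, that 18 leaves no slack, needs none of them except that odd strata are not reconciled across the centre.

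Three stronger readings are tempting, and the document does not support them:
- A reader might infer that the scheme cannot deliver nine per arm. It can, and with blocks of 2 it always does when every stratum is even.
- A reader might take two to three people per stratum as a fact of the design. At 18 enrolled that needs two or three crossed sectors; one sector gives six per stratum.
- A reader might infer biased results or failed stratification. Randomisation remains valid, and with blocks of 2 every stratum is balanced to within one person.

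Severity: minor.

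**What to change.** Allocate each centre in one step once its roster is complete. List the allocations whose arm sizes differ by at most one (9:9 at 18) and that balance profession and sector as closely as possible, then draw one at random. State this in Design in place of the separate stratum lists, so that the group sizes in Procedure follow from the method.

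Include profession as a covariate in the outcome models. As described in Power and Data Analyses, the MANCOVA uses centre, the pre-test and previous contact, and the mixed ANCOVA uses arm, the pre-test and centre; profession, although used in the randomisation, appears in neither.

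The cost is a short script and a paragraph of text. The downside is that the constraint set must be documented and shown to be large enough for the draw to remain properly random. Before the profession and sector constraints, a centre of 18 has C(18, 9) = 48,620 allocations of 9:9; the number left after the constraints should be reported for each centre. If the stratum lists are kept, stating a rule that reconciles odd strata at centre level, or raising the enrolment minimum above 18, would also remove or reduce the mismatch.

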**Figure 1 F1:**
[figure not shown]
Study flowchart.

### Intervention Program

The objective of the program is to reduce negative attitudes and social distance, and increase the inclusive behavior of healthcare workers toward people with SMD.

### Program Development

Focus groups were conducted with people diagnosed with SMD and primary healthcare workers to identify the views that both groups have about how stigma may be expressed in healthcare. This information was used to design the program. Once designed, a panel of experts composed of an academic specialist on the subject, a health professional from PHS, a patient from a PHS with a diagnosis of SMD, a person with SMD who participates in social organizations, an organizational psychologist who specializes in training programs, and a health professional from the secondary level were asked to review it and make suggestions. The program was subsequently implemented as a pilot trial at a healthcare center to refine it and make it more relevant. A manual was developed detailing the protocol for the intervention and explaining the specifics of each activity per session.

The intervention program was designed considering a research approach based on community participation and available background information on strategies that would be most effective. A unique aspect of this intervention is its “ecological” perspective that takes into consideration various structural levels and processes of the social environment and their effect on individual behaviors, thoughts, and emotions both during the formation and subsequent modification of the stigmatization process (67).

### Characteristics and Methods of the Program

The program considers the following levels of intervention:

#### Organizational/structural

The intervention involves aspects of the organizational culture and the structure of the healthcare system that contributes to and influence stigmatization processes (68), such as norms, values, and attitudes (47).

#### Intergroup

Here, the intervention evaluates two central processes: biases derived from group identities (69), and the increase in prejudice associated with contact between social groups having conditions of inequality (70).

#### Individual

At this level, the intervention intends to modify beliefs and attitudes using the social cognitive theory, which is a model based on associative-propositional assessment of attitudes, and the theory of cognitive dissonance (71, 72). In an implementation of the program, a group of participants were people who were diagnosed with a SMD but who had been discharged after their rehabilitation was finished. This organization of people is involved with groups and communities with the objective to reduce stigma.

The program combines strategies for education, contact, and skills development. There will be two meetings with the directors of the healthcare centers, and there will be six sessions with health personnel done on a weekly basis for 2 h per session. The program is run by a healthcare professional and a person who has been diagnosed with SMD.

#### Education strategy

Information is presented about stigma and the consequences it has in several areas, especially in health care. The mistaken beliefs about SMD are disproved, specifically topics dealing with danger and violence, and the irreversibility of the disorder. The information is presented by different sources (people with and without a diagnosis of SMD) and through diverse means (orally, audiovisual, and written).

#### Contact strategy

*Direct contact*: There is direct contact throughout the program because the co-facilitator is someone who has a diagnosis of SMD. In one of the sessions, another person with a diagnosis of SMD shares their life testimony.*Indirect contact*: This is initiated through (i) *videos* in which the participants watch and analyze short videos that show different experiences of people with SMD. The videos show situations of stigma and discrimination that those affected have experienced (with health personnel present), as well as good experiences that have happened to them in the context of their health care; (ii) *written cases* that provide information about a person who has received a diagnosis of SMD for the group to discuss; and (iii) *skills strategy* that teaches skills in a practical and contextualized way on how to accept and resolve difficult situations when dealing with people with SMD. This is performed through role play with real cases that have occurred in the healthcare center. Additionally, verbal and non-verbal communication is addressed.

The sessions are designed to encourage group reflection. The information presented will be discussed and analyzed in groups in a way that favors dissonance and cognitive categorization. Furthermore, the program incorporates effective implementation of non-stigmatizing practices through the planning and execution of behaviors that increase positive attitudes and respectful and inclusive treatment toward people who have SMD (47). The program format emphasizes contact conditions that favor its effectiveness, i.e., status equality between the participants, achievement of common goals, and establishment of a cooperative relationship (52). Furthermore, the contact strategies focus on favoring empathy, which is inversely related to prejudice.

### Program Implementation

Meetings will be scheduled with the directors of the healthcare centers as an encouragement to value the intervention and to facilitate and motivate workers to participate. Thus, it is mandatory that at least one of the meetings be prior to the sessions with healthcare workers. The meetings with the directors are conducted with a methodology similar to that used with the workers. Additionally, there will be a facilitator who is a health professional that has undergone a 20 h contact training process, plus several hours of study of written material regarding SMD and the characteristics and effects of stigma. In addition, all the facilitators for the intervention will be empirically trained. Co-facilitators will be people who have been diagnosed with SMD and they will receive 28 direct hours of training. Training times will be different for the facilitators who are health professionals and those who are diagnosed with SMD; however, there are training times that will be shared between the two groups. During the implementation, the facilitators, and co-facilitators will receive weekly supervision, either online or in person, to evaluate the process and correct any difficulties. The facilitators must complete a weekly checklist of activities to ensure that the program is following the established protocol. Additionally, there will be live supervision in which a member of the research team attends the session but does not participate, and then completes a standardized evaluation form on the session. Afterwards, feedback will be given to the facilitator and co-facilitator about their performance.

### Measurements

#### Social Distance Scale (SD)

Social distance scale (SD) Link et al. (73). This scale evaluates the social distance that people have toward people with SMD. It is composed of a brief vignette where the case of a person with SMD is revealed followed by seven items in a Likert-type response with five alternative answers ranging from disagree to completely agree. The questions are related to different situations that vary in the degree of closeness to the affected person who could be a neighbor, friend, employee, or partner. This scale was adapted and validated for use in the Chilean population (74). The final questionnaire is composed of two factors: “closeness and social interaction” (three items) and “intimacy and trust” (two items). The internal consistency of each of the factors reached Cronbach's alpha values of 0.82 for factor 1, 0.75 for factor 2, and 0.78 for the total scale.

CAMI scale (75). This scale evaluates the attitudes of the general public toward people with SMD. The response is a Likert-type format that is based on five alternatives that range from totally agree to totally disagree. The original scale was adapted and validated for use in the Chilean population (76). The scale is made up of two factors, “acceptance” and “rejection of the installation of mental healthcare centers in the community,” each composed of five items. The internal consistency for each of the factors reached Cronbach's alpha values of 0.61 for the first factor, 0.66 for the second factor, and 0.69 for the total scale.

“Mental Illness: Clinicians' Attitudes” (MICA) scale (77). MICA is a 16-item scale that evaluates the attitudes of professionals and students working in health toward people with SMD. The questionnaire consists of six answer options in a Likert format that ranges from strongly agree to strongly disagree. The internal consistency of the original scale was good (α = 0.72). An adaptation of this scale is being made for validation in the Chilean population.

Self-registration of inclusive behaviors: This is an *ad hoc* scale created to assess self-perception of behaviors that one had toward the last person diagnosed with SMD with whom they had contact. There are 18 items with four response options in a Likert format.

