**STIGMA IN PRIMARY HEALTHCARE WORKERS TOWARD PEOPLE WITH DIAGNOSIS OF SEVERE MENTAL DISORDERS (SMD)**				
Attitudes of the general public toward people with SMD	Community Attitudes to Mental Illness (CAMI) scale	✔	✔	✔
Attitudes of professionals and students working in health toward people with SMD	Mental Illness: Clinicians' Attitudes (MICA) scale	✔	✔	✔
Social distance that people have toward people with SMD	Social distance scale (SD)	✔	✔	✔
Self-perception of behaviors that one had toward the last person diagnosed with SMD with whom they had contact	Self-registration of inclusive behaviors	✔	✔	✔

*T1, assessment before intervention; T2, assessment after intervention; T3, follow-up 4 months after assessment T2*.

Workers assigned to the control group will receive the program once the implementation is completed and the post and follow-up evaluations are finished. A minimum of 11 centers are needed to obtain the required sample size (Table 1).

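### The behaviour scale does not exclude people met through the program, so at T2 treatment itself can change whom experimental-arm workers report on, leaving hypothesis 2 open to bias

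*Protocol article*

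**What the plan says.** The Measurements section of the protocol article describes an ad hoc, 18-item self-report of inclusive behaviours. It assesses "self-perception of behaviors that one had toward the last person diagnosed with SMD with whom they had contact". Table 1 repeats this definition ("Self-perception of behaviors that one had toward the last person diagnosed with SMD with whom they had contact") and schedules the scale at T1, T2 and T3. Neither place limits the person by setting, role or time, and neither excludes program staff. No other behaviour measure is listed, so hypothesis 2 (more inclusive behaviours at post-test and follow-up) rests on this scale.

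The Contact strategy section uses the same notion of contact for the intervention: "There is direct contact throughout the program because the co-facilitator is someone who has a diagnosis of SMD". It adds: "In one of the sessions, another person with a diagnosis of SMD shares their life testimony". This contact is meant to offer "status equality between the participants, achievement of common goals, and establishment of a cooperative relationship".

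On timing, the Procedure section states: "The post-test evaluation (T2) will be done during the 3 weeks following the end of the program". For the other arm, the text after Table 1 states: "Workers assigned to the control group will receive the program once the implementation is completed", and that sentence also places it after the post-test and follow-up evaluations. Under Power and Data Analyses, the covariates are the pre-test score and previous contact with someone with SMD.

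**The concern.** Taken as printed, the definition obliges an attending experimental-arm worker to report on a program person at T2, unless that worker has met someone else with SMD since the last session. A control worker cannot meet such a person through the program before T3. The referent of the outcome is thus affected by treatment after randomization, and in one arm only.

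The plausible direction is toward benefit. The co-facilitator is a trained person met under conditions chosen to make contact go well, whereas a clinic encounter carries no such design. A better score at T2 could then reflect a different counterpart, with no change in how the worker treats the people with SMD met in ordinary practice. That conduct is what the equity rationale of the trial is about.

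Adjusting for the T1 score does not help, because at T1 neither arm has met program staff through the program. The previous-contact covariate does not identify who is reported on at T2 either.

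**Working it through.** **The plan's own figure.** The inputs under Power and Data Analyses are d = 0.5, power 95%, significance level 5% (taken as two-sided) and 105 per group. A two-sample t-test with 105 per arm has power 0.950, so 105 reproduces. This does not bear on the concern, but it gives the sample size used below.

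**Step 1: share reporting on a program person at T2.** The documents do not say how often workers meet other people with SMD, so this rate is an assumption: L contacts per week, arriving at random. T2 is taken as uniform over the 3 weeks after program end. If the last worker session falls g weeks before program end, then for attending experimental-arm workers

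share f = exp(−gL) × (1 − exp(−3L)) / (3L).

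The value of g is not fixed by the documents. There are six weekly worker sessions in an 8-week program that also holds two director meetings, at least one of them before the worker sessions. So g = 0, 1 and 2 are all shown.

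| L per week | f, g = 0 | f, g = 1 | f, g = 2 |
|---|---|---|---|
| 0.1 | 86% | 78% | 71% |
| 0.25 | 70% | 55% | 43% |
| 0.5 | 52% | 31% | 19% |
| 1 | 32% | 12% | 4% |
| 2 | 17% | 2% | 0.3% |

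Example (L = 0.5, g = 0): (1 − exp(−1.5)) / 1.5 = 0.777 / 1.5 = 0.52.

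**Step 2: share at T3.** Four months is about 17.3 weeks, so f = exp(−17.3L). This is 18% at L = 0.1, 1% at L = 0.25 and practically zero above that.

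**Step 3: what a given share could do.** Let s be the score advantage, in standard deviations, of reporting on a program person. The documents give no value, so s is a second assumption. With no true effect, the spurious arm difference is f × s. At s = 0.5, the chance that a two-sided 5% t-test with 105 per arm is significant is:

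| L per week | g = 0: difference | g = 0: chance | g = 2: difference | g = 2: chance |
|---|---|---|---|---|
| 0.1 | 0.43 | 88% | 0.35 | 72% |
| 0.25 | 0.35 | 72% | 0.21 | 34% |
| 0.5 | 0.26 | 46% | 0.10 | 11% |
| 1 | 0.16 | 21% | 0.02 | 5% |
| 2 | 0.08 | 9% | 0.002 | 5% |

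At s = 0.25 and g = 0 the chance runs from 34% down to 6%.

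**Step 4: the same question without a contact model.** Fix f directly, and take the standard error as √[(1 + f(1−f)s²)/105 + 1/105]. The chance of a false benefit is Φ(fs/SE − 1.96), against a nominal 0.025 in that direction. For s = 0.5:
- f = 0.10: difference 0.05, chance 0.055
- f = 0.25: difference 0.125, chance 0.14
- f = 0.50: difference 0.25, chance 0.43
- f = 0 (program people excluded): difference 0, chance 0.025

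Steps 3 and 4 show sensitivity to assumed values. They do not estimate this trial's error rate. They ignore the baseline covariate, the center effect and the multivariate test that comes first.

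**The case against.** **The questionnaire is not shown.** The article gives a short summary of the scale, and the instructions to respondents could already limit the person. That is possible. But both printed definitions are unrestricted, and they are a stated rule, not an omitted detail. If the instrument already excludes program people, only the two descriptions need correcting.

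**The frequency is unknown.** A reader might infer that experimental-arm workers will often report on the co-facilitator. The documents do not support this. Participants are clinical staff in primary care, and the role play uses cases from their own center, so contact at work is to be expected, at an unstated rate. The last worker session may also fall before program end. With two other contacts a week and a two-week gap, the share is below 1%. This objection stands in full as to size.

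**The direction is inferred.** The scale scores the worker's own conduct, not the other person, and its items are unseen. Behaviour toward a co-facilitator in a group of 9 to 20 might score higher, lower or not apply. Benefit is the plausible direction given how the contact is designed, but the documents do not establish it, and the 0.5 standard deviation advantage has no source.

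**The plan tests in sequence.** Outcome-specific analyses follow only after a successful multivariate test. With no true effect on any outcome, and four equally correlated outcomes (assumed correlation 0 to 0.5, no covariates), the 46% case passes that first test 28% to 43% of the time. If attitudes truly improve, however, the first test can be passed on their strength and gives the behaviour outcome no protection.

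**T3 differs from T2.** Hypothesis 2 covers both. A reader might carry the problem over to follow-up, but four months out it largely disappears unless contact is rare.

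**Conclusion.** The concern holds as a defect in a stated definition, mainly at T2. The printed referent lets treatment change, in one arm only, whom the worker reports on, and neither planned covariate repairs this. The T2 comparison for hypothesis 2 is open to bias, plausibly toward benefit.

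It would go too far to say that the result is biased, or to attach one error rate to it. The T2 share runs from 86% to under 1% over the assumed contact rates and session timings. The score advantage needed to turn that share into a bias is not given anywhere. At T3 the share is about 18% at 0.1 other contacts per week and about 1% at 0.25.

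The point still deserves action, because the asymmetry does not depend on those assumptions, the scale is the only behaviour measure, and the problem cannot be undone after data collection unless the person reported on was recorded.

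**What to change.** - Keep the present referent and add one clause to the stem, identically in both arms and at T1, T2 and T3: *not counting anyone you met through the anti-stigma program*.
- Add a *no such contact* option.
- Correct the Measurements text and the Table 1 entry to match.
- Report the number choosing *no such contact* by arm at each time point.

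Optionally, record the approximate date and setting of the contact, so that readers can see what the answers refer to. Limiting the stem to patients of the center is also optional: it is closer to the health-care rationale but narrows hypothesis 2, which concerns people with SMD in general.

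The cost is one sentence of wording before T1, and the sample size does not change. The downside is some missing behaviour scores at T2, likely most where other contact is rarest, which is also where the present wording is most exposed. Because the stem sets no time window, some workers with little contact will also report on an encounter from before the program. That can happen in both arms, and it would dilute a true effect.
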